#### Main outcome measures and statistical analysis plan

Randomly assigned intervention group (standard versus patient-centered) is the main independent variable for intent-to-treat (ITT) analyses. Clinic site is a stratification variable for randomization and is expected to be balanced across intervention groups by design. The primary outcome variable is change in depression symptom severity, upon which we base the sample size evaluation to ensure proper statistical power. Descriptive statistics will be used to describe patient and clinician characteristics at baseline. The comparability of clinician characteristics between intervention groups will be determined for sociodemographic data as well as pre-intervention measures of training, attitudes, management of depression, and communication style. Comparability of patient characteristics between intervention groups will be assessed with regard to pre-intervention sociodemographics, depression level, health status measures, and other key variables. Variables found to be unbalanced between intervention groups will be adjusted for in all ITT analyses. Adherence to the intervention (*e.g*. number of intervention visits kept) will be considered as a covariate in subsidiary, on-treatment analyses.

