The data on outcome variables fall into two broad categories: continuous variables, such as depressive symptom score (CES-D) [48] and functional status scores (MOS SF-12) [49], and dichotomous variables, such as depression remission status and receipt of guideline-concordant treatment. The primary ITT analyses are designed as regression modeling using patients as the unit of analysis, with each regression model structured to have a parameter designated for each visit where the outcome of the model was scheduled to be assessed, separately for each intervention group, so that the mean model is fully saturated for the intervention by visit parametrization. This parametrization allows estimation of mean differences observed within each intervention group betweeen baseline and a given follow-up visit for a continuous outcome, and odds ratios of having the outcome event at a given follow-up versus the baseline visit within each intervention group for a binary outcome, after adjusting for other covariates in the model. The evalution of patient-centered intervention effects will be conducted by testing the significance of difference of the adjusted mean differences, or the ratio of adjusted odds ratios, of a given follow-up versus the baseline visit between the intervention groups. The primary testing contrast is the baseline to 12-month change in outcomes between intervention groups; the models can easily accommodate additional data obtained by extending the follow-up to 18 months.

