Site and clinician characteristics are included as covariates in all regression models to account for potential patient outcome clustering within clinical sites and/or clinicians. To account for longitudinal correlations between outcome assessed over time within patients, mixed effects modeling appraches with unstructured correlation matrix are used whenever possible. Robust estimation is used for statistical inferences. The likelihood approach underlying the proposed mixed effects modeling would produce valid statistical inferences with missing data if the missing mechanism is Missing at Random (MAR) and the proposed mean and correlation models are correct. We thus anchor our ITT analyses on mean models with fully saturated visit by intervention parametrization plus all the covariates as necessary, paired with an unstructured correlation model to develop valid statistical inferences under MAR. We then conduct sensitivity analyses through multiple imputation under plausible missing scenarios that are non-MAR to examine the robustness of our inferences under such situations.

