#### Sample size considerations

One of the major hypotheses to be tested is that improvements in CES-D scores for depressed patients in the patient-centered intervention group will be greater than those in the standard intervention group. Previous studies of treatment of depression in primary care using similar interventions (excluding the patient-centered and cultural adaptations) have shown remission and symptom improvement differences between intervention and usual care groups of 20 to 30% [19,20]. Our resources and available recruitment pools allowed us to aim for 15 clinicians and 125 patients per group, with an average number of 8.3 patients per physician (cluster). By assuming a within-cluster or intra-class correlation of 0.1 [50] and 15% dropouts by the end of 12 months follow-up (reflected using the variance inflation factor), a correlation between the baseline and 12 month CES-D score of 0.5, a mean CES-D score of 30 points at baseline for both intervention groups, 25% score reduction (*i.e*., 7.5 points) by 12 months in the standard intervention group, and the common cross-sectional SD for CES-D of 10 points for both intervention groups at both visits, we would have 80% statistical power to detect a between-group difference of 3.6 points or more in improvement in mean CES-D score at one year using a two-sided test with Type I error of 0.05. That is, if we expect to see a 7.5 point improvement in mean CES-D score for the standard intervention group after one year, then we would have 80% power to detect a 11.1 points or greater improvement in mean CES-D score for the patient-centered intervention group after one year.

Ethics and Consent

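### The primary contrast is a valid but inefficient difference in change; prespecified adjustment for baseline CES-D would be more precise, by about 25% of variance at patient level and by an amount that depends on clustering in this design

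*Protocol article*

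**What the plan says.** All places are in the Protocol article.

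- **Main outcome measures and statistical analysis plan, mean model.** Each regression has one parameter per scheduled visit, "separately for each intervention group, so that the mean model is fully saturated for the intervention by visit parametrization".
- **Same section, contrast.** "The primary testing contrast is the baseline to 12-month change in outcomes between intervention groups".
- **Same section, covariance.** The saturated mean is "paired with an unstructured correlation model to develop valid statistical inferences under MAR".
- **Same section, covariates.** Baseline depression severity is among the characteristics compared between arms. The rule is then: "Variables found to be unbalanced between intervention groups will be adjusted for in all ITT analyses". Baseline CES-D is not otherwise a covariate, and the arms' baseline means are not set equal.
- **Sample size considerations.** The trial is powered on the difference in improvement, with "a correlation between the baseline and 12 month CES-D score of 0.5" and a "common cross-sectional SD for CES-D of 10 points for both intervention groups at both visits".

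**The concern.** When each arm has its own baseline mean, the model cannot use the expectation that the arms start alike. The contrast then subtracts the whole observed baseline difference. Only part of that difference predicts the 12-month score: half of it, at a correlation of 0.5 with equal SDs. Subtracting the rest adds noise.

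Precision is scarce in this trial. It enrolled 132 patients against a target of 250, and the baseline CES-D SD was 14.09 against the assumed 10. The Discussion accepts that power may be compromised. The baseline score that would recover some precision is already collected.

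**Working it through.** **Inputs** (Sample size considerations): SD 10 at both visits; correlation r = 0.5; ICC 0.1; 8.3 patients per clinician; 125 patients per arm; 15% dropout; 80% power; "two-sided test with Type I error of 0.05". The multiplier is 1.960 + 0.842 = 2.802.

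**1. The plan's own figure.** The article claims "80% statistical power to detect a between-group difference of 3.6 points or more in improvement in mean CES-D score at one year". The detectable difference is 2.802 × √(2 × V × DE / n), where V is the variance per patient and DE the design effect.
- Change score, V = 2 × 10² × (1 − 0.5) = 100, without clustering or dropout: 2.802 × √(200/125) = 3.54.
- With DE = 1 + 7.3 × 0.1 = 1.73 and n = 125 × 0.85 = 106.25: 5.06.
- Of the readings tried, only one uses every stated input and returns 3.6. It multiplies the change variance by (1 − ICC): 2.802 × √(2 × 100 × 0.9 × 1.15/125) = 3.605.

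Whether 3.6 is right is a separate question. The present point does not depend on it.

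**2. Patient-level variance, complete data.**
- Change: 2 × SD² × (1 − r) = 100.
- Baseline-adjusted: SD² × (1 − r²) = 75.
- Ratio: (1 + r)/2 = 0.75, a 25% reduction. It would be 35% at r = 0.3 and 15% at r = 0.7.

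**3. Does the unstructured covariance already recover this?** No. A generalised-least-squares information matrix was computed for three visits, 100 patients per arm, all correlations 0.5 (the 6-month correlations are assumed).

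| | Arm-specific baseline means | Baseline information used | Reduction |
|---|---|---|---|
| Complete data | 2.000 | 1.500 | 25% |
| 15% lost after baseline | 2.265 | 1.765 | 22% |

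The second column was computed with a common baseline mean. A baseline covariate gives the same values here: 2 × 75/100 = 1.500 and 2 × 75/85 = 1.765.

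**4. Clustering.** The article gives no correlation of clinician effects between baseline and 12 months, so this is an assumed range. Split the variance of 100 into 10 between clinicians and 90 within. A clinician mean then has variance 10 + 90/8.3 = 20.84. If c is the covariance of the baseline and 12-month clinician means, the change variance is 2 × (20.84 − c). The adjusted variance with slope b is 20.84 × (1 + b²) − 2bc. The slope is taken as the within-clinician slope, as 0.5, or as the best slope for clinician means.

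| Clinician effects over time | c | Change variance | Adjusted variance | Reduction |
|---|---|---|---|---|
| Independent | 6.02 | 29.64 | 19.10 to 20.58 | 31-36% |
| Correlate 0.5 | 10.42 | 20.84 | 15.63 | 25% |
| Fully stable | 14.82 | 12.05 | 10.31 to 11.79 | 2-15% |

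Detectable differences with 106.25 per arm:
- correlating 0.5: 5.06 falls to 4.38;
- fully stable: 3.84 falls to between 3.56 and 3.80.

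Under the (1 − ICC) reading that returns 3.6, the reduction is about 2-13%.

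**5. As enrolled (illustration).** Assume 66 patients per arm, 15% dropout (n = 56.1), ICC 0.1, SD 14.09 at both visits, r = 0.5, clinician effects correlating 0.5 over time, and 28 contributing clinicians (36 less eight). Then DE = 1 + (132/28 − 1) × 0.1 = 1.37, and the detectable difference falls from about 8.7 to 7.6 points.

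**The case against.** **The plan is coherent.** The outcome, the tested contrast and the powered quantity are all change. A reader might infer that the change contrast is biased or invalid. The documents do not support that; the loss is one of precision only.

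**The 25% is not a fixed figure for this trial.** A reader might infer a flat 25% saving, or one third more patients needed (100/75). Either holds only with complete data and clinician effects that correlate over time as patients' scores do. Stable clinician effects cancel in a change score, which is a real advantage of the planned contrast in a cluster trial. This objection stands and sets the lower end of the range. It does not reverse the direction: every case examined shows some gain.

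**The as-enrolled figures are not trial facts.** Clinicians split 15 and 21, patient numbers per arm are not given, and 14.09 is a baseline SD only.

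**Changing the model is not free.** The section on data collection says follow-up was extended after 12-month follow-up was complete, because improvement patterns had differed between arms. A new primary contrast would therefore be chosen with some knowledge of results. This stands and shapes the fix.

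**Baseline differences may not be pure chance.** Patients were recruited after their clinicians were randomised, and some were nominated by them. Masked recruiters reduce this risk but do not remove it. It counts against forcing a common baseline mean more than against a baseline covariate.

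**The plan may already adjust for baseline depression.** It does so only if imbalance is found, with no stated criterion. That is not prespecified adjustment.

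**Conclusion.** The point holds as an efficiency weakness in a method that the article fixes. At r = 0.5 and equal SDs, baseline adjustment lowers the patient-level variance by 25% with complete data and by about 22% with 15% dropout in the likelihood model. At trial level the gain runs from about 2% to about 36%. Where it falls depends on the stability of clinician effects, and the article does not support a single figure. The conditional covariate rule does not secure the gain, and neither does the unstructured covariance. The change is worth making because the data are in hand and the sample fell well short of target.

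**What to change.** For CES-D and the SF-12 scores:

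- Make the 6- and 12-month scores the response. Include baseline score and baseline-by-visit as fixed covariates whatever the observed balance, with arm by visit, site and clinician clustering. The primary contrast is the arm difference at 12 months.
- Prefer the baseline covariate to a common-baseline-mean constraint, because recruitment followed clinician randomisation.
- Date the change, justify it on the planned correlation of 0.5 and not on observed results, and disclose that 12-month patterns by arm had been seen. Report the planned change contrast alongside.
- State any expected gain as a range over the stability of clinician effects. List the assumptions beside any as-enrolled detectable difference.

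The cost is a model re-specification and its disclosure. No new data are needed.

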#### Specific aim two

Compare the effectiveness of the patient-centered intervention with the effectiveness of the standard intervention by evaluating their impact on the following patient outcomes at six and 12 months: depression symptom reduction; depression remission; functional status improvement; and receipt of guideline-concordant treatment.

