#### Eligibility criteria

Clinicians recruited for the BRIDGE study were general internists, family physicians, and nurse practitioners who saw patients at least 20 hours per week at one of the participating study sites. The clinicians were recruited without regard to race, gender, or age. Patients had to be between the ages of 18 and 75 years and report their race or ethnicity as African American; they had to be positive on a screener for major depressive and dysthymic disorder from the CIDI [30], which identified individuals who reported two weeks or more during the last year and one week or more during the past month when they felt sad, empty, depressed, or lost interest in things they normally enjoyed. The screener was self-administered with assistance as needed at the time of the recruitment visit. In addition, screen-positive patients had to meet criteria for one-year major depression on a subsequent structured interview [30], defined as: meeting DSM-IV criteria for MDD in the past year [31]and having symptoms present for at least one week in the past month, to be considered eligible for the study. Patients were excluded if they had an acute life-threatening condition or cognitive impairment that prevented them from completing the screener; indicated they did not intend to receive care in the clinic on an ongoing basis; had no access to a telephone; were currently pregnant, breastfeeding, or less than three months postpartum; screened positive for current bereavement, lifetime mania, or current alcohol or drug abuse; did not speak English; were currently receiving specialty mental health care; or reported immigrating to the United States within the preceding five years.

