**Questionnaires**				

Sociodemographics	X		X	X
Age, sex, race/ethnicity, education, income, employment^1^, health insurance^1^, financial stress^¶^				

Attitudes, beliefs, and other behavioral measures	X	X	X	X
Trust in health professionals, preferred role in decision-making, depression treatment preferences, spirituality, respect, perceived involvement in care^2^, racial identity, social support, life events				

Health Status	X	X	X	X
Physical and mental, measured by MOS-SF12, CIDI^3 ^&ES-D, psychiatric co-morbidity^4^, disability days				
Healthcare Utilization	X	X	X	X
Mental healthcare utilization (receipt of antidepressant medication and/or counseling) General healthcare utilization (emergency room visits and hospitalizations)				
Healthcare Process	X	X	X	X
PDM with providers, visit-specific and overall satisfaction, satisfaction with case manager^5^, ratings of depression care management and intervention materials^6^				

**Audiotapes **(patient-provider communication)^7^	X			

CIDI = Composite International Diagnostic Interview, Depression Scale, CES-D = Center for Epidemiologic Studies Depression Scale, PDM = participatory decision making; ^1^measured at 12 and 18 months; ^2^measured only at 18 months; ^3^not measured at six months; ^4^Substance abuse, panic attacks, anxiety, and traumatic events; ^5^measured only at six and 12 months; ^6^measured only at 12 months only; ^7^collected at enrollment visit and after primary care provider intervention.

One modification to the original study protocol was made shortly after the 12-month follow-up was complete. Because the pattern of improvement differed between intervention groups at six months and 12 months of follow-up, a decision was made to extend follow-up to one additional interview at 18 months, and IRB approval was obtained to re-contact study patients. However, because outcomes assessors at 18 months were not blinded to intervention assignment, depression status at 12 months remains the study's primary outcome.

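### Remission is tested as change from baseline although every patient entered with MDD: not estimable if remission is CIDI-based, and blurred and usually less precise if it is a CES-D cut-off

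*Protocol article*

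**What the plan says.** The section on main outcome measures and the statistical analysis plan divides outcomes into continuous variables and "dichotomous variables, such as depression remission status and receipt of guideline-concordant treatment". Each model has one parameter per arm for every scheduled visit, baseline included. For binary outcomes the within-arm quantity is "odds ratios of having the outcome event at a given follow-up versus the baseline visit within each intervention group for a binary outcome", and the between-arm test is on "the ratio of adjusted odds ratios, of a given follow-up versus the baseline visit between the intervention groups". On timing, "The primary testing contrast is the baseline to 12-month change in outcomes between intervention groups".

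The eligibility section requires "meeting DSM-IV criteria for MDD in the past year" on a structured interview, plus symptoms for at least a week in the past month. The patient baseline section reports that 42 people were ruled out by the second-stage CIDI.

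Aim two lists "depression symptom reduction; depression remission; functional status improvement" among outcomes to be compared at six and 12 months. A footnote to Table 4 says the CIDI was "not measured at six months". The CES-D has no such exception. The article gives neither an instrument nor a threshold for remission.

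**The concern.** A change-from-baseline contrast suits an outcome that can vary at baseline. Remission from a disorder that every patient had to have in order to enrol may not vary at all. If nobody can be in remission at entry, the reference odds are zero in both arms, and the quantity to be tested divides one undefined ratio by another. Software would then report a separation artefact or stop.

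Remission is part of the main hypothesis in the Abstract and is listed in aim two, so its test should work under whichever definition is used. The visit schedule adds a second difficulty: a CIDI-based definition cannot deliver the six-month comparison that aim two announces.

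**Working it through.** The article states no remission rate, odds ratio or power, so there is no figure of the plan's own to reproduce. The check asks whether the stated contrast exists and how well it is estimated under each possible definition.

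**Inputs from the article.** Enrolled patients: 231 eligible for the second-stage screen − 35 refused − 22 not reached − 42 ineligible = 132. Baseline CES-D: mean 29.84, SD 14.09 (Table 6).

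**Assumptions, not in the article.** 66 patients per arm; 12-month remission of 26/66 and 40/66 (about 40% and 60%); CES-D cut-offs of 10 and 16; clinician clustering ignored.

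**1. Remission as no longer meeting the CIDI entry definition.**
- Baseline odds = p0/(1 − p0) = 0/1 = 0 in each arm.
- Each within-arm odds ratio is (follow-up odds)/0, so their ratio has no value.
- A saturated arm-by-visit logistic model fitted to such data gives a visit coefficient of 24.14 (SE about 16,126) and an interaction of 0.86 (SE about 22,806). The size of the visit coefficient depends only on where the iterations stop, and a Wald test of the interaction is meaningless.
- At six months there are no CIDI data.

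**2. Remission as a CES-D cut-off: share already below it at entry.**
- Cut-off 16: Φ((16 − 29.84)/14.09) = Φ(−0.98) = 0.163, about 22 of 132.
- Cut-off 10: Φ((10 − 29.84)/14.09) = Φ(−1.41) = 0.080, about 10 or 11 of 132.
- Truncating the normal distribution at zero lowers these to 0.148 and 0.064. With the planning values (mean 30, SD 10) they would be 0.081 and 0.023.

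**3. Precision under a CES-D cut-off.** Take 11/66 remitted at baseline in each arm, close to the 16% above.
- Follow-up variance of the log odds per arm: Vf = 1/26 + 1/40 = 0.0635.
- Baseline variance per arm: Vb = 1/11 + 1/55 = 0.1091.
- Follow-up only: log odds ratio = ln[(40/26)/(26/40)] = 0.86 (odds ratio 2.37), SE = √(2 × 0.0635) = 0.36.
- Baseline-referenced, visits treated as uncorrelated: the same 0.86, SE = √(2 × (0.0635 + 0.1091)) = 0.59. The variance ratio is 0.345/0.127 = 2.7.
- With within-patient correlation ρ, the per-arm variance is Vf + Vb − 2ρ√(Vf·Vb). It falls below Vf only if ρ > ½√(Vb/Vf) = ½√(0.1091/0.0635) = 0.66.
- At ρ = 0.3 the SE is √(2 × (0.1726 − 0.6 × 0.0832)) = 0.50, still above 0.36.
- Binary outcomes with these margins cannot reach 0.66. The largest possible ρ is √[(11/55) × (40/26)] = 0.55 in the arm with 26 remitted, and √[(11/55) × (26/40)] = 0.36 in the arm with 40.

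**4. Other outcomes.** Eligibility does not fix treatment at entry: 101 of 132 (76.5%) were taking an antidepressant. The same contrast is therefore not degenerate by design for guideline-concordant treatment. The CES-D mean change is unaffected.

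**The case against.** The strongest reply is that the article never ties remission to the CIDI, and an article may leave that definition to a fuller document. The CES-D is scheduled at enrolment and at six, 12 and 18 months, so a CES-D threshold would serve every visit at which remission is claimed and would make the contrast finite. A reader might infer that the remission analysis is undefined outright. The text does not support that, and this part of the reply stands.

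The CIDI case also needs care. Entry required MDD within the past year plus recent symptoms, not full criteria at the time of enrolment. Clinician-nominated patients were at various stages of care. A CIDI rule about current full criteria could therefore give some remission at baseline; zero follows only if the entry definition itself is reused as the outcome. Nor does the missing six-month CIDI break the model, which has only "a parameter designated for each visit where the outcome of the model was scheduled to be assessed". It conflicts with aim two, and only under a CIDI definition. Finally, in a saturated model with empty baseline cells, the follow-up cells still allow a between-arm comparison at 12 months, so failure to converge is not certain.

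Under a CES-D cut-off, the planned contrast is a legitimate difference in differences on the log-odds scale in a randomised comparison. The objection to it concerns interpretation and efficiency, not validity.

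What the reply does not remove is that the article fixes a method and applies it to remission by name. The complaint is not that a definition is absent. It is that the stated contrast suits this population poorly under either natural definition.

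**Conclusion.** The point holds in conditional form. If remission means no longer meeting the CIDI entry definition, baseline remission is 0 of 132, the planned contrast is not estimable at any follow-up visit, and six-month remission has no data. If remission is a CES-D cut-off, the contrast can be estimated. It then treats about 8% to 16% of patients enrolled with MDD as remitted at entry, and it is generally less precise than a follow-up-only comparison (SE 0.59 against 0.36 with no within-patient correlation). Those figures rest on the assumed cut-offs, normal scores and illustrative 12-month rates given above.

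Severity is moderate. A reader might infer that the trial's primary analysis is at risk, because the paragraph on the 18-month extension calls depression status at 12 months the primary outcome. The analysis section, however, names change in symptom severity as the primary outcome variable, and the sample size rests on CES-D change. Neither that analysis nor the guideline-concordant treatment outcome is affected.

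**What to change.** For remission only, take the baseline visit out of the outcome vector. Compare arms on remission at follow-up, with 12 months as the main contrast and baseline CES-D as a covariate. This restores an estimable comparison under a CIDI definition. Under a CES-D cut-off it drops a sparse baseline cell that mainly adds noise.

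State the remission definition and match it to the schedule. Either use an instrument collected at every visit where remission is claimed, or limit CIDI remission to visits where the CIDI is measured and amend the six-month claim in aim two to agree. If remission is CES-D-based, aim two can stay as it is.

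The cost is a change of wording in the analysis plan and a simpler model for one outcome. No new data are needed. How clinician clustering is modelled is a separate question that this change does not touch.

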#### Randomization

Randomization was stratified by study site and conducted at the clinician level with patients sequentially selected within each randomized clinician (10 patients from each clinician). Within each study site (stratum), a randomization schedule was generated through computer by the study statistician using the Moses and Oakford algorithm [32]with the block sizes of two or four randomly created in a four to one ratio. Informed consent and baseline data collection from clinicians (background questionnaire and videotaped interview with the standardized patient) were completed before participating clinicians were randomly assigned (using a blind and secure allocation by computer) to either the standard or the patient-centered intervention. At the screening visit, patients of enrolled clinicians provided oral consent to complete the screening questionnaire. Once eligibility was confirmed, written consent and screening visit data were collected. Additionally, study staff obtained permission from eligible patients to contact them several times over the next 12 months. Patients were then assigned to the standard or patient-centered intervention according to their clinicians' randomization status. The patient recruiters were blinded to the clinicians' randomization assignment during recruitment, and the patients did not know their assigned treatment status until after enrollment. Due to the behavioral nature of the interventions, blinding or masking of study participants, investigators, and depression care managers was not possible. However, interviewers who collected baseline and follow-up data from patients at six and 12 months were masked to clinician and patient intervention assignment.

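### Clinician clustering is assigned to covariates, which cannot carry it; unless the unspecified robust variance is taken at clinician level, the primary standard error is too small whenever clinicians differ in their patients' change

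*Protocol article*

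**What the plan says.** Under Randomization: "Randomization was stratified by study site and conducted at the clinician level". Patients take the assignment of their clinician.

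Under Main outcome measures and statistical analysis plan, three statements bear on correlation, after the opening one that "The primary ITT analyses are designed as regression modeling using patients as the unit of analysis":

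- Clinician and site level: "Site and clinician characteristics are included as covariates in all regression models to account for potential patient outcome clustering within clinical sites and/or clinicians".
- Patient level: "To account for longitudinal correlations between outcome assessed over time within patients, mixed effects modeling appraches with unstructured correlation matrix are used whenever possible".
- Variance: "Robust estimation is used for statistical inferences". The level at which this is done is not given.

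The mean model has one parameter per visit and intervention group, and the primary test compares the groups on change from baseline to 12 months. The same section makes validity with missing data depend on the mean and correlation models being right.

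Under Sample size considerations, the planning counts the clinician level: "By assuming a within-cluster or intra-class correlation of 0.1", with 15 clinicians and 125 patients per group.

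**The concern.** Each source of correlation is given its own device. Repeated visits within a patient get an unstructured correlation. Patients of the same clinician get fixed covariates. No clinician random effect, clinician-level GEE or clinician-clustered variance is named.

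A covariate such as specialty or years in practice can remove only the part of the between-clinician variance that it explains. The rest stays in the errors as if patients of one clinician were independent. The sample size thus counts a correlation that the described analysis has no stated place for. If the robust variance is taken over patients, the primary p-value is too small and the confidence interval too narrow.

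This is not a detail left to a fuller analysis plan. The article states which method handles the clustering, and that method does not do so.

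**Working it through.** **Inputs.** ICC 0.1, 15% dropout, SD 10 at both visits and a baseline-to-12-month correlation of 0.5 (Sample size considerations). 132 patients and 36 randomised clinicians (Abstract). One clinician left before baseline data collection and eight contributed no patients (Baseline characteristics of the clinicians). The reasons listed for the eight add to 3 + 1 + 3 = 7. If the early leaver is the eighth, 28 clinicians contributed; if not, 27. Both are used.

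**The plan's own figures.** Planned cluster size: 125/15 = 8.33, as stated. The detectable difference of 3.6 points does not reproduce. With DE = 1 + (8.3 − 1)(0.1) = 1.73, n = 125 × 0.85 = 106.25 per group and SD of change √(2·100·(1 − 0.5)) = 10, it is (1.960 + 0.842)·10·√(2·1.73/106.25) = 5.06. That is a separate matter, and the 3.6 is not used below.

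**Step 1: what covariates do for the tested contrast.** Write the mean for group g at visit v as μ(g,v) + βx, with x a site or clinician characteristic constant over visits. With complete data and a common unstructured covariance, the fitted μ(g,v) equals the group mean at that visit minus β̂ times the group mean of x. In μ(g,12) − μ(g,0) the β̂ term drops out, so the contrast is the same with or without x. A generalised least squares check agreed (three visits, 28 clinicians split 12/16 by assumption, 132 patients). A covariate explaining 60% of the clinician variance in change moved the estimate by less than 1e-14, and type I error was 11.3% both with and without it.

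Covariates act on change only if interacted with visit, which the article does not state. Suppose they were, at an ICC of change of 0.1 and 28 clinicians. In two simulations, three clinician covariates explaining 0%, 30% and 60% of the clinician variance left type I error at about 11%, 9 to 11% and about 8%.

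**Step 2: size if the variance ignores clinicians.** DE = 1 + (m − 1)·ICC; actual type I error = 2·[1 − Φ(1.96/√DE)]. With the ICC of change at 0.1:

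| Setting | m | DE | 1.96/√DE | Type I error |
|---|---|---|---|---|
| 132 over 28 | 4.71 | 1.371 | 1.674 | 9.4% |
| 132 over 27 | 4.89 | 1.389 | 1.663 | 9.6% |
| 112.2 (15% dropout) over 28 | 4.01 | 1.301 | 1.719 | 8.6% |
| 112.2 over 27 | 4.16 | 1.316 | 1.709 | 8.8% |
| Planned | 8.33 | 1.733 | 1.489 | 13.7% |

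For the enrolled sample, intervals are too short by 1 − 1/√1.371 = 14.6% to 1 − 1/√1.389 = 15.1%.

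**Step 3: if 0.1 is cross-sectional.** The clinician variance is 0.1 × 100 = 10 at each visit. Let c be the correlation of the clinician effect between baseline and 12 months, which the article does not give. The clinician variance of change is 2·10·(1 − c) and the total variance of change is 100, so the ICC of change is 0.2(1 − c). For 132 patients over 28 and 27 clinicians:

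| c | ICC of change | Type I error |
|---|---|---|
| 1 | 0 | 5.0% |
| 0.9 | 0.02 | 5.9% |
| 0.8 | 0.04 | 6.7–6.8% |
| 0.5 | 0.10 | 9.4–9.6% |
| 0 | 0.20 | 13.8–14.2% |

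**Step 4: if the robust variance is clustered on clinician.** With 28 clinicians, an ICC of change of 0.1 and a normal reference, simulation (2,000 runs) gave 6.8% without clinician covariates and about 9% with three acting on change. Most of the clustering is then covered, but a small-sample correction is still needed.

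**The case against.** The strongest reply is the sentence on robust estimation. It names no level, and a regression with patients as rows is compatible with a sandwich variance clustered on clinician. If that was meant, the clinician correlation is in the standard errors. A reader might infer that the plan certainly leaves it out and so certainly inflates type I error; the text does not support that. What remains is that the article assigns clustering to covariates and correlation modelling to visits within a patient, so nothing points to a clinician-level sandwich. Even then, Step 4 shows that the small number of clusters needs handling.

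Second, the tested quantity is a change, so a clinician effect constant over time cancels. The article does not give an ICC of change separately. It applies 0.1 while sizing for improvement in CES-D, which favours Step 2 but does not settle it. This objection stands as a limit on the size: 9.5% is one point in a range that includes no inflation.

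Third, the enrolled figures use all 132 patients, and the clinician count is derived. Dropout lowers the result to about 8.7%; the choice between 27 and 28 hardly matters.

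A reader might also infer that the site covariates should go, because they use up scarce between-clinician degrees of freedom. That does not follow: site stratified the randomisation and belongs in the model.

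**Conclusion.** The point stands, conditionally. The stated device for clinician clustering cannot represent residual correlation within clinician, and as main effects it leaves the primary contrast essentially untouched. This is wrong as written.

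Its effect on the primary test depends on two things the article leaves open: the level of the robust variance, and how far clinicians differ in their patients' change. With a patient-level variance and an ICC of change of 0.1, type I error is about 9.5% as enrolled, about 8.7% after 15% dropout and 13.7% at the planned cluster size. With 0.1 read as cross-sectional, the enrolled range is 5% to about 14%. With a clinician-level variance, only the small-sample problem remains. These are formula values for equal cluster sizes; in simulation with unequal sizes and an ICC of 0.1, the patient-level test rejected in about 10 to 11% of runs.

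**What to change.** Keep the saturated visit-by-group longitudinal model and keep site as the stratification covariate. Replace the sentence saying that covariates account for clustering with one of these:

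- (a) A clinician-by-visit random effect, with Kenward-Roger or Satterthwaite degrees of freedom. A clinician intercept constant over visits is not enough, because it cancels from the change contrast. Clinician as a fixed effect is not available either: clinicians are nested in intervention group, so clinician-by-visit terms would absorb the group contrast.
- (b) A robust variance stated to be clustered on clinician, with a small-sample correction such as CR2 and a t reference based on the number of clinicians.

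Use an equivalent clinician-level correction for remission and guideline-concordant treatment. Unweighted GEE would generally need a stronger missing-data assumption than the likelihood approach the plan relies on, so say how missing data are handled if GEE is chosen. Clinician characteristics may stay as prognostic covariates, but not as the clustering device. Report the estimated ICC, for change as well as cross-sectionally.

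The cost is a short change of wording, some extra model code and somewhat wider, correct intervals. At an ICC of change of 0.1, the standard error grows by a factor of √1.371 = 1.17 to √1.389 = 1.18 over one that ignores clinicians, before the small-sample correction.
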